## Abstract

**Background:**

Despite high levels of clinically significant persistent cancer related fatigue in breast cancer survivors few treatments are currently available and most pose a significant burden on the part of the woman. Acupressure, a component of Traditional Chinese Medicine, has been shown to decrease fatigue levels by as much as 70% in cancer survivors while being inexpensive, non-toxic and an easy to use intervention. The primary aim of this study was to determine the efficacy of two types of self-administered acupressure (relaxation acupressure and stimulating acupressure), compared to standard of care on fatigue severity. Secondary aims were to evaluate the efficacy of two types of acupressure on sleep and kinetic parameters required for implementation of acupressure in a clinical setting; The purpose of this paper is to share the methodology used including challenges and insights.

**Methods/design:**

This study is a three group, randomized clinical trial. 375 breast cancer survivors at least 12 months after completion of cancer treatments, with moderate to severe persistent fatigue, are being randomized to one of 3 groups: self-administered relaxation acupressure; self-administered stimulating acupressure; or standard of care. Participants are assessed at baseline, 3 weeks, and 6 weeks followed by a 4-week follow-up period. The primary aim is to examine the effect of 6-weeks of relaxation acupressure compared to stimulatory acupressure or standard of care on fatigue as assessed by: weekly self-report using the Brief Fatigue Inventory; objective daytime physical activity on actigraph; or fatigue patterns assessed 4-times daily using a visual analog scale. Secondary endpoints include depression, anxiety, self-efficacy, and sleep quality.

**Discussion:**

This study has the potential to develop a low-cost, self-care intervention for the most troubling of late-term effects in breast cancer populations, fatigue. The methods used may lend constructive ideas to other investigators working with this population and/or intervention.

**Trial registration:**

ClinicalTrial.Gov Trials Register NCT01281904

## Background

 There are nearly 3 million breast cancer survivors in the US
[1]. Persistent cancer-related fatigue (PCRF) is one of the most distressing symptoms experienced by breast cancer (BC) survivors
[2,3]. Rates of PCRF in BC survivors range from 30% to 82% and persist for as long as 10 years after diagnosis
[3-7]. PCRF is associated with decreased quality of life,
[5,6,8] and decreased sleep quality
[5,6]. Beyond poor quality of life, subjective reports of low levels of fatigue, at diagnosis, in BC survivors predict longer recurrence-free and overall survival even after adjusting for key clinical and socio-demographic confounders
[9]. Thus, decreasing the burden of PCRF could lead to a positive impact on women’s quality of life as well as improve their clinical status. Currently, however, there are few treatment options for PCRF.

Acupressure is a technique derived from acupuncture, a component of Traditional Chinese Medicine (TCM). In acupressure, physical pressure is applied to acupuncture points by the hand, elbow, or with various devices to treat disease. Acupressure has several advantages over other potential PCRF treatments: it is self-administered with little effort and time on the part of the patient; it is well tolerated; low-cost; and requires minimal instruction by clinic staff, e.g., nurse. Pilot randomized controlled trials (RCT) have demonstrated that self-administered acupressure can significantly decrease PCRF by as much as 70% from baseline levels in cancer survivors
[10]. Acupressure can also have positive effects on sleep quality
[11,12] and sleep quantity
[10,12] in cancer patients and other chronically ill populations, but the degree to which these sleep improvements influence improvements in PCRF has not been explored. In a pilot clinical trial, Zick and colleagues
[13] found that relaxation acupressure (RA) reduced PCRF more than stimulatory acupressure (SA), although PCRF was reduced by both treatments. In a separate study, Harris and colleagues
[14] showed that sleepiness was increased to a greater degree following RA compared to SA. Based on these findings we designed a RCT to investigate the effect of self-administered acupressure on PCRF and sleep in a large group of breast cancer survivors. Below is an outline of our study design.

### Study aims and hypotheses

The hypothesis of this project is that self-administered RA will result in improvements in measures of PCRF, quality of life, and sleep quality, compared to SA and standard of care. To assess this hypothesis, our primary aim is to examine the effect of 6-weeks of RA compared to a regimen of SA or standard of care on fatigue as assessed by:

A. weekly self-report using the Brief Fatigue Inventory (BFI), our primary outcome.

B. objective daytime physical activity on a wrist worn accelerometer using average activity counts/minute.

C. fatigue severity assessed 4 times daily using a visual analog scale recorded on wrist-worn accelerometer.

D. quality of life as assessed by Long Term Quality of Life Instrument (LTQL).

Our secondary aims include investigating the effect of 6-weeks of RA compared to a regimen of SA or standard of care on sleep quality of BC survivors as assessed by:

A. monthly self-report using the Pittsburgh Sleep Quality Index (PSQI), our primary outcome.

B. daily sleep/wake diaries and nighttime actigraphy.

C. examining the relationships between improvements in sleep quality and improvements in quality of life for SA and RA, as assessed by LTQL.

Our other secondary aim is to assess activity parameters required for implementation of an acupressure treatment in a clinical setting including the time to onset of a clinically meaningful effect as well as the duration of effect following cessation of the intervention. These factors are currently unknown for acupressure.

## Methods/design

### Study design

This is a randomized parallel group clinical trial with three study arms. The study schema and estimated recruitment numbers are presented in Figure
1. The study was approved by the University of Michigan Medical School Institutional Review Board and participants provided written informed consent.

**Figure 1 F1:**
[figure not shown]
Flow of Participants Through the Study.

### Study participants

The study participants are female breast cancer survivors (stage 0-IIIa), aged 18 years and older who were at least 12 months post-treatment and had a complaint of persistent, moderate to severe fatigue despite standard treatments. We detail eligibility criteria along with source of that material and the study personnel responsible for determining that criteria in Table
1. One of the principal investigators, who is a physician, reviews all eligibility documents and determines a woman’s suitability for participating in the study.

**Table 1 T1:** Eligibility Criteria vs. Source Document

**Criteria**	**Source**	**Assessor**
Female breast cancer survivors	Medical Records, Michigan Tumor Registry, Medical History & Physical Exam	Study Nurse, Study Coordinator
Cancer free	Medical Records, Michigan Tumor Registry, Medical History & Physical Exam	Study Nurse, Study Coordinator
Completed treatment (i.e., surgery, chemotherapy, radiotherapy, immunotherapy, etc.) at least one year prior	Medical Records, Medical History & Physical Exam	Study Nurse, Study Coordinator
Capable of self-administering acupressure	Observation at screening visit	Study Nurse, Study Coordinator
Complaint of fatigue	Brief Fatigue Inventory score of ≥ 4	Study Nurse, Study Coordinator
Pregnant or planning to become pregnant	Pregnancy test, Medical History & Physical Exam	Study Nurse, Study Coordinator
Fatigue causing comorbidities (e.g. anemia, fibromyalgia diagnosis prior to breast cancer)	Medical Records, Medical History & Physical Exam	Study Nurse, Study Coordinator
Medication changes	Review of Concomitant Medications, Medical History & Physical Exam	Study Nurse, Study Coordinator
Acupuncture/Acupressure w/in 6 months	Communication with potential participant	Study Coordinator
Non-Breast cancer diagnosis w/in 10 years	Medical History & Physical Exam	Study Nurse
Medications for insomnia	Medical Records, Review of Concomitant Medications	Study Nurse, Study Coordinator
Untreated major depressive disorder and suicidal ideations	PRIME-MD (‘several days’ indicated on question 2i)	Study Nurse, Study Coordinator
Final, overall eligibility	Potential participant’s final review of eligibility	Principal Investigator

### Randomization, blinding and allocation concealment

This is a single-blinded study. Participants, investigators, study nurses and all study staff are blinded. However, the nurses who teach the acupressure will know if participants are assigned to the standard of care arm or one of the two acupressure arms. The randomization scheme was created by the study statistician. Within each county under study, eligible patients are being randomized into one of these three groups: RA, SA or standard of care in a 1:1:1 ratio for a target total of 375 patients.

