### Recruitment and enrollment challenges

There are multiple steps to obtaining an adequate sample size for an RCT consisting of cancer survivors. They are often no longer in the formal care system and must be located via alternative means. In the acupressure study, participants are identified through the Michigan Tumor Registry (MTR), which is run by the Michigan Department of Community Health (MDCH). The registry collects information about cancer incidence, stage, and to a limited extent, the kinds of treatment that patients receive. These data are reported to the registry from oncology facilities statewide. The MTR also includes cancer case information received from the metropolitan Detroit Surveillance, Epidemiology, and End Results (SEER) registry. The Michigan Cancer Surveillance Program, which operates the Michigan Tumor Registry, is a member of the North American Association of Central Cancer Registries (NAACCR). The registry is certified by NAACCR as meeting all standards for quality, completeness, timeliness, and unresolved duplicate records (1 per 1000 tumors) and is estimated to be greater than 95% complete based on external audit findings.

The initial step is for the study team was to obtain Institutional Review Board (IRB) approval from the universities involved as well as the MTR. Next, the study team worked collaboratively with the staff at the MTR to clarify the population of interest. MTR Data were requested for women diagnosed between January 1st, 2006 and December 31st, 2010, from 5 counties in Michigan (Wayne, Washtenaw, Ingham, Genesee, and Kent). These counties represent significant population centers (Detroit, Ann Arbor, Lansing, Flint, and Grand Rapids), and areas of racial and ethnic diversity.

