## Acupressure intervention

The study utilizes individual instruction by acupressure educators to teach study participants about the acupressure intervention. Acupressure educators are local study staff (located in the county where the women are being recruited from the cancer registry) made up of nurses who have been trained by one of the study co-principal investigator (Co-PI), who is a professional acupuncture practitioner. The study Co-PI meets with the local acupressure educators for an initial training session. At this session he explains the basic philosophy of TCM and acupressure, demonstrates both sets of study acupressure points on himself and on the educator. He also gives the educators a DVD of a person performing the acupoints, laminated illustration of acupoints along with a written description of where the points are located. He also asks the educators to demonstrate the correct location of the acupoints on themselves as well as proper pressure and stimulation techniques.

The Co-PI makes a site visit to observe the acupressure educator performing both sets of acupoints (stimulating and relaxing) on themselves. He notes how many acupoints are correctly located and makes any needed corrections. He also asks them to apply the correct amount of pressure and stimulation on a point on him. The Co-PI has a checklist that interveners must match at a 95% rate. After the acupressure educator has enrolled two participants, the Co-PI returns to the site to check for the efficacy of the acupressure educators and then twice yearly afterwards. These assessments of the acupressure educators are how we measure their treatment fidelity. Acupressure educators can request additional clarification and instruction as needed.

From our previous study, participants can be taught to perform their acupoints within 15 minutes
[13]. Acupressure educators meet with each participant separately and demonstrate the location of each acupoints on themselves and on the participants. Participants also have the acupoints marked on them with adhesive colored dots to reinforce the location of the acupoints for the first few days. At the end of the session participants are asked to demonstrate the location of all their acupoints to the educator and appropriate adjustments are made.

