## Statistical issues

### Statistics and power analysis

Primary Aim: The primary aim of this study is to investigate the differential effects of different modes of acupressure on fatigue in breast cancer survivors. For this, we are focusing on three fatigue outcomes, namely, BFI, which will be administered weekly, a measure of average daily physical activity and a self-reported fatigue score, both based on Actiwatch-S data. A BFI is collected weekly and provides a measure of average degree of fatigue, a score that ranges between 0 and 10, with higher numbers indicating more fatigue. We will be analyzing the BFI outcome over phases. The first phase BFI is obtained by averaging week-1 to week-3 measures (mid-treatment). The second phase comprising of week-4 to week-6 measures indicates the status in the second half of the treatment phase (end-treatment). The final phase comprises of week-7 to week-10, the washout phase (washout). In order to investigate the change in BFI between the three study arms, we are using a mixed-effects regression analysis with average BFI in the three phases as the outcome, phase as the within-subjects factor, and group (RA, SA, standard of care) as the primary between-subjects factor. The baseline BFI level will be used as a covariate. We shall further adjust the model for key demographic variables such as age and ethnicity, as well as the baseline HADS score. A *subject* random-effect will be used to account for the clustering effect within the three measurements on the same subject. Of primary interest is the group*phase interaction, the significance of which will indicate differences in extent of decrease between the arms. Post-hoc analyses of phase difference within each arm will be carried out multiple comparison adjustment. Model diagnostics will be carried out to confirm the distributional assumptions and appropriate corrective actions (e.g. transformation) will be performed as needed.

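### Women are randomized within county, but no stated analysis model includes county; the cost is a small, conservative loss of precision for between-group contrasts in the linear models

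*Protocol article*

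**What the plan says.** **Allocation.** Randomization, blinding and allocation concealment states "Within each county under study, eligible patients are being randomized into one of these three groups", with the three arms, ending in "standard of care in a 1:1:1 ratio for a target total of 375 patients". Recruitment and enrollment challenges says that registry data were requested "from 5 counties in Michigan (Wayne, Washtenaw, Ingham, Genesee, and Kent"). No block size or other balancing method within county is given, and no other stratification factor is mentioned.

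**Primary model.** Statistics and power analysis describes a mixed-effects regression of phase-average BFI with "phase as the within-subjects factor, and group (RA, SA, standard of care) as the primary between-subjects factor". It continues: "The baseline BFI level will be used as a covariate", and then "We shall further adjust the model for key demographic variables such as age and ethnicity, as well as the baseline HADS score". The only random effect is for subject: a "random-effect will be used to account for the clustering effect within the three measurements on the same subject". The group-by-phase interaction is named as the test of primary interest.

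**Other models.** The same section carries this framework or covariate set over to daytime activity, the fatigue visual analog score (VAS-F), the logistic model for severe BFI, the quality-of-life change-score model, the PSQI models and the time-to-onset model. Sleep onset and time to relapse follow by analogy. County is not a fixed effect, a random effect or a stratum in any of them, and it is not in the power model.

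**County as delivery unit.** Study visits take place in county extension offices. The nurses who teach acupressure are local staff, "located in the county where the women are being recruited from the cancer registry".

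**The concern.** A factor that governs allocation is normally carried into the analysis. When balance is forced within strata, each county contributes nearly equally to every arm, so differences between counties cancel from a comparison of arms. A model without county does not know this. It leaves the between-county variance in the error term and reports an arm contrast as less precise than it is. Intervals are then a little too wide and tests reject a little less often than 5% under the null. Because visits and teaching are organised by county, it is plausible that county has some relation to outcome.

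This touches the stated aim even though the interaction is the headline test. All three phases come after randomization and baseline BFI is a covariate, so a benefit that is already present in the first phase and stays level shows in the group effect, not in the interaction. The protocol's own power scenario contains such a pair: standard care at 4 then 4, and stimulating acupressure at 3 then 3. The change is zero in both arms and the whole difference is a group effect. The Power analysis section also reports power for the difference between groups.

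**Working it through.** **Inputs from the Power analysis section.** BFI means for standard care, stimulating and relaxation acupressure are 4, 3, 3 at mid-treatment and 4, 3, 2 at end-treatment. The two variances are 4 and 4 with intra-class correlation 0.5, read here as subject variance 4 and residual variance 4. There are 100 women per arm and the level is 5%. Stated power is more than 0.95 for group and 0.82 for the interaction, from 100 simulations.

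**Input not in the documents.** The share ρ of the variance of a woman's mean score that county explains. It is assumed to lie between 0 and 0.10.

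**1. The plan's own figures.**
- Group effect: subject means are 4, 3, 2.5, with sum of squared deviations 1.167. The variance of a subject mean is 4 + 4/2 = 6. The noncentrality is 100 × 1.167/6 = 19.44 on 2 and 297 degrees of freedom, giving power 0.98. This agrees with the stated figure.
- Interaction: changes are 0, 0, −1, with sum of squared deviations 0.667. The variance of a change is 2 × 4 = 8. The noncentrality is 100 × 0.667/8 = 8.33, giving power 0.73, not 0.82. At 125 per arm (375/3) it is 0.83. The Monte Carlo standard error of 0.82 from 100 simulations is √(0.82 × 0.18/100) = 0.038, so its 95% interval is 0.745 to 0.895. This gap is a separate matter: county enters neither calculation.

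**2. Between-group contrasts in a linear model, balance forced within county.** The true contrast variance is (1 − ρ) times what the model without county assumes. Hence:
- SE ratio (without county / with county) = 1/√(1 − ρ)
- actual size of a nominal 5% pairwise test = 2 × [1 − Φ(1.96/√(1 − ρ))]
- noncentrality of the group test with county = 19.44/(1 − ρ), on 2 and 293 degrees of freedom

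| Assumed ρ | SE ratio | Pairwise size without county | Group power with county |
|---|---|---|---|
| 0 | 1.000 | 0.050 | 0.982 |
| 0.01 | 1.005 | 0.049 | 0.983 |
| 0.02 | 1.010 | 0.048 | 0.984 |
| 0.05 | 1.026 | 0.044 | 0.986 |
| 0.10 | 1.054 | 0.039 | 0.990 |

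Group power computed without county is 0.982 throughout, so the largest difference is 0.8 of a point.

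**3. Simulation check.** 2000 runs per setting, 300 women, permuted blocks of three within five counties of assumed size 90, 60, 51, 51 and 48, and an additive county effect. Each cell gives the result without / with county.

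| ρ | Type I error, group | Power, group | Power, interaction |
|---|---|---|---|
| 0 | 0.049 / 0.049 | 0.980 / 0.980 | 0.734 / 0.733 |
| 0.05 | 0.050 / 0.055 | 0.990 / 0.991 | 0.726 / 0.726 |
| 0.10 | 0.036 / 0.048 | 0.985 / 0.989 | 0.735 / 0.735 |

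The simulated group test has 2 degrees of freedom, for which the large-sample size without county is 0.05^(1/(1 − ρ)): 0.043 at ρ = 0.05 and 0.036 at ρ = 0.10. The simulation matches at 0.10. At 0.05 it does not settle the question, because the Monte Carlo standard error is √(0.05 × 0.95/2000) = 0.005.

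**4. Interaction.** If county c adds the same amount u to a woman's score in every phase, her change between phases contains u − u = 0. County therefore drops out whether or not it is in the model, as the last column shows.

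**The case against.** The strongest objection is that the test of primary interest is not affected. That stands for any county effect constant over phases. Only a county-by-phase effect would alter it, and a county main effect would not address that.

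The second is that the mismatch in standard errors needs balance forced within county, and the article states no blocking. That also stands. Allocating 1:1:1 within county suggests such balance but does not establish it. Under simple randomization within county, the model without county has a valid standard error and only forgoes precision.

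The third is that 1/√(1 − ρ) is a linear-model result. In logistic and hazards models, adding a prognostic factor changes the quantity estimated and generally does not shrink the standard error of the coefficient. No gain in precision is claimed for those models.

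The fourth is that the covariate list is open and the analysis plan is not shown. This stands only in part. The open wording qualifies demographic variables, and a randomization stratum is not naturally one of them. The article also sets out its fixed and random effects in enough detail for the absence of county to be a feature of the stated model.

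A reader might also infer that county adjustment would remove differences between nurse-educators. The documents do not support that. They do not say there is one educator per county, and educators teach only the acupressure arms, so their differences are largely arm-specific and an additive county factor would not remove them.

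**Conclusion.** The point holds as a modest mismatch between design and analysis. County is the only stated stratum and no stated model uses it. With allocation balanced within county, the linear models (BFI, activity, VAS-F, PSQI) give between-group standard errors about 0.5% to 5% too wide for an assumed county share of 1% to 10%. The figure is smaller once baseline BFI, and perhaps ethnicity, absorbs part of the county difference. The error is on the safe side: type I error is at or below 5%.

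Three stronger readings are tempting and not supported. The omission does not invalidate or weaken the interaction test, for the reason in step 4. It does not leave the trial short of power for the group effect. It does not explain why the stated interaction power of 0.82 fails to reproduce at 100 per arm.

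The size rests on an assumed county variance, since the documents give none, and on an additive county effect. It is worth correcting because a steady benefit is read from the group effect and because the change costs almost nothing.

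**What to change.** - Add county as a five-level fixed factor to the BFI model and to the linear models that reuse its covariates (activity, VAS-F, PSQI, quality-of-life change scores).
- Include county in the logistic and discrete-time survival models so that they match the allocation, without claiming narrower intervals.
- Stratify the proportional hazards model by county.
- If county is to be left out, say why. In either case, state whether allocation within county is blocked.

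The cost in the linear models is 5 − 1 = 4 degrees of freedom, for example 297 to 293 for the group test at 100 per arm. County is known for every woman at randomization, so no new data are needed and only the analysis wording changes. Naming county in advance also removes a later, data-driven choice about adjusting for it.
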